## Abstract

**Background:** There is consistent evidence that community and clinical samples of individuals with an alcohol use disorder (AUD) have attentional biases toward alcohol cues. The alcohol attentional control training program (AACTP) has shown promise for retraining these biases and decreasing alcohol consumption in community samples of excessive drinkers. However, there is a lack of evidence regarding the effectiveness of ACTP in clinical AUD samples. The main aim of the present study is to investigate whether primary pharmacological and psychological, evidence-based alcohol treatment can be enhanced by the addition of a gamified AACTP smartphone application for patients with an AUD.

**Design and Methods:** The study will be implemented as a randomized controlled trial. A total of 317 consecutively enrolled patients with AUD will be recruited from alcohol outpatient clinics in Denmark. Patients will be randomized to one of three groups upon initiation of primary alcohol treatment: Group A: a gamified AACTP smartphone application + treatment as usual (TAU); Group B: a gamified AACTP sham-control application + TAU; or Group C: only TAU. Treatment outcomes will be assessed at baseline, post-treatment, and at 3- and 6-month follow-ups. Repeated measures MANOVA will be used to compare the trajectories of the groups over time on alcohol attentional bias, alcohol craving, and drinking reductions. It is hypothesized that Group A will achieve better treatment outcomes than either Group B or Group C.

**Perspectives:** Because attentional bias for alcohol cues is proportional to the amount of alcohol consumed, and these biases are not addressed within current evidence-based treatment programs, this study is expected to provide new evidence regarding the effectiveness of the gamified AACTP in a clinical population. Furthermore, due to promising results found using AACTP in community samples of excessive drinkers, there is a high probability that the AACTP treatment in this study will also be effective, thereby allowing AACTP to be readily implemented in clinical settings. Finally, we expect that this study will increase the effectiveness of evidence-based AUD treatment and introduce a new, low-cost gamified treatment targeting patients with an AUD. Overall, this study is likely to have an impact at the scientific, clinical, and societal levels.

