##### Alcohol Attentional Bias

Patients' AB for alcohol cues will be assessed using the alcohol Stroop task. The task consists of two categories of words presented in different font colors (i.e., red, yellow, blue, and green): (1) alcohol-related words (e.g., bar, beer, rum, scotch, tequila, vodka, whisky), and (2) neutral words (e.g., ceiling, cupboard, fence, gate, shed, tap, chair). The two categories of words are matched for word frequency and length, number of syllables, and semantic relatedness. As in the classic Stroop task, the patient's task will be to name the color in which the words are presented while attempting to ignore the meaning of the words. AB is indicated by longer reaction times to the alcohol-related words relative to the neutral words (27, 32).

In this study, the alcohol Stroop task with pictures will also be used to measure patients' AB for alcohol cues, thereby indicating whether patients have benefitted from the AACTP training. To determine this, the task will consist of pictures of alcoholic and non-alcoholic beverages, each presented with colored outlines (i.e., red, yellow, blue, or green): (1) pictures of alcoholic beverages (e.g., beer, wine, spirits), and (2) pictures of non-alcoholic beverages (e.g., water, orange juice, smoothie). Alcohol AB is indicated by longer reaction times to the alcohol cues than to the non-alcoholic cues (24).

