#### Clinical Outcomes

##### Primary Outcome Measures

Alcohol consumption will be measured with the Alcohol Timeline Follow-back (TLFB) method. It involves using a calendar to help the patient retrospectively recall the number of drinks that he/she consumed on each day during the previous 3 months (59, 72). The results will be used to calculate various alcohol consumption measures, including weekly mean drinking, which will be the primary outcome measure.

To validate the TLFB, hair samples from the patients will be tested for ethyl glucuronide (ETG) by liquid chromatography-tandem mass spectrometry (LC-MS/MS). This biological marker of alcohol consumption will be collected and analyzed according to the Society for Hair Testing (73, 74).

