### Statistical Analysis

The intent-to-treat principle will be followed in the analyses to evaluate the intervention. A repeated-measures MANOVA with groups as the between-participants factor and assessment time-point as the within-participants factor will be used to test the efficacy of the intervention across the assessment points. Efficacy would be indicated by a significant Time X Study Group interaction. Each of the significant interactions will be followed up with *post-hoc* tests to identify the source of the interaction. Potential demographic covariates (e.g., age, education, income) will also be considered by using MANCOVA. Further, attrition rate at each follow-up time point will be evaluated. Baseline characteristics of participants who remain in the study will be compared with those who have been lost to follow-up. A multiple imputation (MI) approach that adjusts for uncertainty arising from missing data (76, 77) will also be conducted to evaluate the main findings.

Based on MacKinnon (78) mediational procedures, a series of regression analyses will be conducted to test the hypothesized mediational relationships among the outcome variables, i.e., that reductions in *alcohol AB* and *cravings* will partially mediate improvements in the outcome measures. Several ancillary interaction effects will also be evaluated, although they are not hypothesized to be significant. They include potential interactions between the intervention received and patients' drinking history, affective states, and cognitive flexibility. Although the intervention is intended to be effective for all AUD patients, it is important to test this assumption by evaluating whether the intervention is effective for specific sub-groups of patients.

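### The efficacy rule is not tied to weekly mean drinking, so as written a change in attentional bias or craving alone can be reported as efficacy

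*Protocol article*

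**What the plan says.** The Measures and Primary Outcome Measures sections give a clear designation. Several consumption measures will be derived from the timeline follow-back, "including weekly mean drinking, which will be the primary outcome measure". Craving, self-efficacy and affect are secondary, and readiness to change is listed with them under Secondary Outcome Measures. Attentional bias sits in a third class, the experimental measures, taken only at baseline and post-treatment. The clinical measures are taken at all four assessments.

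The Statistical Analysis section does not carry that designation into its decision rule. It states: "Efficacy would be indicated by a significant Time X Study Group interaction. Each of the significant interactions will be followed up with" post-hoc tests to locate the source. The second of these sentences expects more than one such result. The abstract says what the repeated-measures MANOVA is for: to "compare the trajectories of the groups over time on alcohol attentional bias, alcohol craving, and drinking reductions". The second paragraph of Statistical Analysis gives bias and craving a different role, as partial mediators of improvement in the outcomes.

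**The concern.** The trial asks whether adding the app makes treatment for alcohol use disorder more effective, and the protocol's chosen yardstick is drinking. A rule that accepts any significant interaction among bias, craving and drinking does not answer that question.

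Attentional bias is the process the app sets out to train. The picture Stroop, with coloured outlines around drink pictures, resembles Level 2 of the training. A group difference there shows that the training reached its target. It does not show that patients drank less. The protocol's own citations suggest that the two can part: the unpublished study in detoxified drug users is quoted with f = 0.39 for bias but 0.18 for number of relapses.

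A mediator should not also serve as proof of the effect it is supposed to transmit. Two readers applying the present sentence to the same data could reach opposite conclusions on efficacy.

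**Working it through.** **Inputs from Statistical Analysis.** α = 0.05; three groups; four time-points; planning f = 0.20; target power 0.90; 264 analysed (88 per group); prior f = 0.30 for bias and 0.37 for weekly mean drinking, from the same source. **From Measures.** Bias is assessed twice.

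**Assumptions of this check.** f is the effect on the change from baseline to post-treatment. Group A differs and B = C. Drinking and craving have no effect. Correlation between outcomes is 0 unless stated.

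**The plan's own figure.** For the within-between interaction by Pillai's V: s = min(3−1, 4−1) = 2, df1 = 2 × 3 = 6, df2 = 2 × (264 − 4) = 520, λ = N·s·f² = 264 × 2 × 0.04 = 21.12. Power is 0.950. The same formula gives N = 221 at power 0.90, so the stated 264 matches 0.95, not 0.90. That is a separate matter. Here it shows only that 264 is ample for one outcome at f = 0.20.

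**Separate tests: bias alone.** With two time-points the interaction is a one-way ANOVA on change: df = 2 and 261, critical F = 3.03, λ = N·f².

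- f = 0.30: λ = 264 × 0.09 = 23.76, probability of significance 0.9945.
- f = 0.20: λ = 264 × 0.04 = 10.56, probability 0.833.

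**Separate tests: any of the three significant.** If drinking and craving are null and independent, the probability is 1 − (1 − p) × 0.95².

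- f = 0.30: 1 − 0.0055 × 0.9025 = 0.995.
- f = 0.20: 1 − 0.167 × 0.9025 = 0.849.

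Simulation (4,000 trials, 3 × 88 patients, drinking and craving null over four time-points) gave 0.995 and 0.858.

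**One joint test of three change scores** (Pillai trace, simulated). The shift in Group A that gives f is f × 3/√2, that is 0.64 SD for 0.30 and 0.42 SD for 0.20.

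| Bias effect | Any separate test | Joint test | Drinking test alone |
|---|---|---|---|
| f = 0.30 | 0.995 | 0.97 | about 0.05 |
| f = 0.20 | 0.85–0.86 | 0.66–0.68 | about 0.05 |
| none | 0.14 | about 0.05 | about 0.05 |

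At a correlation of 0.3 between outcomes the joint figures rise to 0.99 and 0.74.

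**No effect on anything.** Three independent tests at 0.05 give 1 − 0.95³ = 0.143; correlation between outcomes lowers this somewhat.

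**The case against.** The strongest reply is that the hierarchy exists. One primary outcome is named, craving and the scales are secondary, bias is an experimental measure, and bias and craving are described as mediators. With a single named primary outcome, many readers would take the efficacy test to apply to it. Bias, with two assessments, does not fit the four-time-point model that was powered. Per-outcome tests would show which outcome moved, so a bias-only result would be visible beside a null result on drinking.

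Much of this stands, and it limits the point. A reader might infer that the protocol has no outcome hierarchy; it has one, and the fault is that the decision sentence does not use it. The reply does not remove the fault, because the abstract names bias and craving as MANOVA outcomes and the rule expects several interactions. The post-hoc tests come only after the rule has been met. The two-assessment argument does not exclude clinical craving, which is measured at all four time-points.

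Three further inferences are tempting and unsupported:

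- **That the rule will almost certainly misfire.** This needs a bias effect of f = 0.30 or more, cited from sub-clinical drinkers, and a zero effect on drinking where the same source reports f = 0.37.
- **That error rates for larger sets of outcomes apply.** The eight response variables belong to the dosage power analysis, not to the efficacy test. Multiplicity adjustment of secondary outcomes may properly be left to an analysis plan.
- **That the picture Stroop is presented as clinical efficacy.** The phrase "thereby indicating whether patients have benefitted from the AACTP training" can fairly be read as a check that the training changed its target.

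**Conclusion.** The point holds as a fault in a stated rule, not as a missing detail. The sentence that yields the efficacy conclusion is not linked to weekly mean drinking, and the abstract brings bias and craving within its reach.

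The size is conditional. If drinking is unchanged and bias moves by f = 0.30, the rule is met in about 99% of trials with separate tests or 97% with a three-outcome joint test. At f = 0.20 this is about 83–86% and 67%. A rule confined to drinking would be met in 5%. With no effect anywhere, three separate tests give up to about 14%, while a joint test stays near 5%. The figures rest on reading f as the effect on change, on 264 analysed patients, and on assumed correlations between outcomes. They show what the wording allows; they do not forecast the trial's result. The change should be made, and it is a matter of wording.

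**What to change.** Replace the efficacy sentence in Statistical Analysis with, for example: *Efficacy will be concluded only from the Time × Group test on weekly mean drinking (timeline follow-back), analysed in its own model. Attentional bias is a mechanism outcome. Craving, self-efficacy, readiness to change and affect are secondary, supportive outcomes. Interactions on any of these do not by themselves establish efficacy.* Bring the abstract's sentence on the MANOVA into line.

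No extra patients are needed: by the formula above, 264 analysed give about 95% power at f = 0.20 for drinking alone. The one real cost is that a result positive only on bias or craving can no longer be called efficacy.

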### Aims

The main aim of the study is to determine whether a gamified version of the AACTP when used as an add-on to a primary evidence-based treatment will increase the treatment's effectiveness. Based on the available evidence, it is hypothesized that the experimental group (Group A) will achieve a better treatment outcome than either the active control group (Group B) or the treatment-as-usual group (Group C). Additionally, we hypothesize that there will be a dose-response effect in Group A: the more that the patients use the AACTP, the better their outcome will be. Full descriptions of the experimental and control groups are provided in Section 2.5 below.

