A power analysis (79, 80) was conducted using G^*^Power for a repeated-measures MANOVA with α = 0.05; effect size (ES) of *f* =0.20; power = 0.90; groups *k* = 3; and time-points measurements = 4. It showed that 88 participants will be required for the final analyses in each of the four cells (total *N* = 264). Prior evaluations identified *f* s of 0.30 (AB) and 0.37 (weekly mean drinking) and an *f* of 0.42 (situational confidence to resist drinking) on outcome measures for sub-clinical excessive drinkers (36). Further, in a study that used the intervention as an add-on treatment for clinical participants with a substance-use disorders other than AUD, effect sizes of *f* s = 0.33 (drug-specific AB), 0.34 (number of relapses), 0.32 (temptation to use) and 0.37 (self-confidence to resist temptation) were identified (42). Also, an unpublished study conducted with detoxified drug-abusers found *f* s of 0.39 (drug-specific AB), 0.18 (number of relapses), and 0.35 (temptation to use) (81). A second power analysis for a MANOVA with special effects and interactions was conducted to test the dosage-effect across groups (α = 0.05; EF *f*
^2^(*v*) = 0.06; power = 0.90; *k* = 3; predictors = 3; and response variables = 8), which yielded an *N* of 220. Attrition in similar studies has usually ranged from 10 to 15% (41, 42). Assuming a somewhat higher attrition rate (20%), which is not unlikely (82, 83), indicates that 317 (264 + [264·0.20]) participants should be tested at baseline for an analysis using listwise deletion of missing cases, although a multiple imputation (MI) analysis will also be conducted to verify that results converge across missing data assumptions. The projected sample size is sufficient for the planned data analyses, including mediational analyses based on Fitz and MacKinnon's guidelines (84).

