## Discussion

The present study will investigate whether (1) the AACTP as an add-on intervention increases the effectiveness of a primary evidence-based treatment, and (2) a gamified version of AACTP can be successfully delivered *via* a smartphone application as an add-on. As mentioned in the introduction, the alcohol ACTP has been evaluated in community samples of excessive drinkers, for whom reductions in AB and alcohol consumption were observed post-treatment and at follow-up (32, 36, 37). In the first experimental study, it was found that individuals with harmful alcohol use (drinking > 50 units per week for men and > 35 units per week for women) showed reductions in both AB and alcohol consumption at post-treatment, and these reductions were maintained at a 3-month follow-up (32). In this initial study, the participants served as their own controls, which is a commonly used method in an initial evaluation of a new intervention (85). Hence, after recruitment and assessment, there was, in accordance with this alternative tradition, a waiting period before ACTP was started, and during this period there was no change in either AB or alcohol consumption, but there was a decline in both measures following the introduction of the AACTP intervention 1 month later (32). Similarly, a second randomized controlled study of a sub-clinical sample of hazardous drinkers (22–50 units per week for men and 15–35 units per week for women) and persons with harmful alcohol use found that the ACTP (compared to a non-active control group) was effective in decreasing alcohol consumption at post-treatment and at the 3-month follow-up, but the reductions had attenuated at the 6-month follow-up (36). A third randomized controlled study investigated whether the AATCP could be successfully delivered *via* a fully automated web-based delivery pathway to a community sample of hazardous drinkers. At post-intervention, a reduction in both alcohol craving and alcohol consumption was found in the AACTP group compared to an active sham-control group. However, the effects on alcohol consumption were not maintained at the 3-month follow-up (37). Finally, a fourth study tested a gamified AACTP delivered though a smartphone application in another community sample of hazardous drinkers (18–40 years old). Results indicated that reductions of up to 40% in alcohol consumption had occurred several months after the training (86).

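### The efficacy criterion is a non-directional three-arm Time x Group interaction, so meeting it does not establish that Group A is better than Group B and better than Group C

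*Protocol article*

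**What the plan says.** The Aims section of the protocol article gives a directional hypothesis about two comparisons: "the experimental group (Group A) will achieve a better treatment outcome than either the active control group (Group B) or the treatment-as-usual group (Group C". Under Primary Outcome Measures, the endpoint is "weekly mean drinking, which will be the primary outcome measure".

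The Statistical Analysis section then names the test: "A repeated-measures MANOVA with groups as the between-participants factor and assessment time-point as the within-participants factor will be used to test the efficacy". The decision rule follows: "Efficacy would be indicated by a significant Time X Study Group interaction". The next sentence adds: "Each of the significant interactions will be followed up with *post-hoc* tests to identify the source of the interaction". It names no contrast and no direction, and it does not make the efficacy conclusion depend on the result.

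The sample size paragraph in the same section powers the repeated-measures MANOVA (alpha 0.05, f = 0.20, power 0.90, three groups, four time points, 264 analysed). A second calculation covers the dosage effect. No power is given for A versus B or for A versus C.

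**The concern.** The written rule and the hypothesis answer different questions. The interaction test rejects when any arm's trajectory differs from another's, in either direction. It would be satisfied by a sham arm that does worse while A matches treatment as usual, by an A arm that does worse than both others, or by two app arms that do equally well and both beat treatment as usual.

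The last pattern matters for this design. The article's section on the sham application says that arm is there to separate re-training of attention from the effect of extra attention or being studied. A result with A equal to B shows no training-specific effect, yet it meets the efficacy criterion. What is at stake is whether a positive primary test can be read as support for the stated hypothesis. As written, it cannot.

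**Working it through.** **Inputs from the Statistical Analysis section.** Alpha 0.05, f = 0.20, k = 3 groups, m = 4 time points, N = 264 (88 per arm).

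**Assumptions, not in the article.** The MANOVA is applied to weekly mean drinking alone. SD is 1 at each visit and the correlation between visits is 0.5. An arm that differs is shifted by a constant d at all three post-baseline visits, with d from 0.4 to 0.6.

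**Step 1: the plan's own figure.** For the interaction by Pillai's trace, s = min(k-1, m-1) = 2 and df1 = (k-1)(m-1) = 6. Then df2 = s(N-k-(m-1)+s) = 2 x (264-3-3+2) = 520.
- Noncentrality N x s x f² = 264 x 2 x 0.04 = 21.12 gives power 0.950.
- The alternative df2 x f² = 520 x 0.04 = 20.8 gives 0.947.
- Power 0.90 needs N = 221 or 225 respectively, so 264 is not reproduced as the size for 0.90. The difference is on the generous side and does not affect this point.

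**Step 2: what 0.20 means for one contrast.** On the MANOVA scale, f² = V/(s-V), so V = 2 x 0.04/1.04 = 0.0769. If the effect lies in one direction, the single root is 0.0769/(1-0.0769) = 0.0833, and its square root is 0.289.
- One arm differs from two equal arms: d = 0.289 x 3/√2 = 0.61 SD of the contrast variable. Power for A versus B at 88 per arm, two-sided 0.05, is 0.98.
- B lies midway between A and C: the step is 0.289/√(2/3) = 0.354 SD, and power for A versus B is 0.65.

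This agrees with the simulation scale. Mean change from baseline has variance (1 + 2 x 0.5)/3 + 1 - 2 x 0.5 = 0.667, so SD 0.816, and a shift of 0.5 gives 0.5/0.816 = 0.61.

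**Step 3: how often the written rule is met.** Simulation with 88 per arm, 2,500 runs per scenario:

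| True state | d = 0.4 | d = 0.5 | d = 0.6 |
|---|---|---|---|
| A better, B = C | 0.809 | 0.958 | 0.995 |
| Only sham worse, A = C | 0.816 | 0.953 | 0.995 |
| A worse, B = C | 0.802 | 0.950 | 0.995 |
| A = B, both better than C | 0.810 | 0.950 | 0.996 |

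With no difference anywhere, the rule is met in 0.050 of runs. The rows agree within simulation error because the test ignores sign and arm labels. That symmetry does not depend on the assumed correlation.

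**Step 4: a rule that matches the hypothesis.** Success requires A significantly better than B and than C on mean change from baseline, each two-sided 0.05:

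| True state | d = 0.4 | d = 0.5 | d = 0.6 |
|---|---|---|---|
| A better, B = C (power) | 0.843 | 0.968 | 0.997 |
| Only sham worse, A = C | 0.031 | 0.023 | 0.028 |
| A worse, B = C | 0.000 | 0.000 | 0.000 |
| A = B, both better than C | 0.022 | 0.024 | 0.026 |

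Keeping the interaction as a gate before these contrasts lowers power to 0.752, 0.940 and 0.993.

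**The case against.** The strongest reply is that the efficacy sentence should not be read alone. The direction is in the Aims, and post-hoc tests follow any significant interaction. Read together, this is a conventional omnibus gate followed by comparisons judged against a stated hypothesis. With three arms and one outcome at one time point, that sequence also controls the familywise error. Much of this stands. The 0.95 is the chance of a significant interaction, not the chance that the authors would report benefit after looking at the arms. The reply does not repair the rule, because the criterion is met before the post-hoc tests run and those tests are only diagnostic.

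Four stronger readings are tempting, and the documents do not support them.
- **The trial would announce efficacy for a harmful app.** The post-hoc step makes that unlikely. No passage reports harm from the sham either. It directs attention to alcohol on half its trials, but its stated aim is an equal split. The scenarios show what the rule cannot distinguish; they are not forecasts.
- **The contrasts are underpowered.** Low figures (0.80 for A versus B and 0.69 for both with B = C; 0.37 for A versus B with B midway) arise only if 0.20 is read as Cohen's f for a single comparison, while the omnibus figure reads it on the MANOVA scale. On one consistent scale, A versus B has 0.98 when B = C. The 0.65 needs B midway, a pattern the article does not state.
- **Effects are known to fade.** The Discussion does say of one trial that "the effects on alcohol consumption were not maintained at the 3-month follow-up". It also describes one study with reductions maintained at 3 months, one effective at 3 months and attenuated at 6, and one with reductions several months after training. The evidence is mixed.
- **Test order and multiplicity control are missing.** An article may leave these to the analysis plan.

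**Conclusion.** The point holds as a mismatch between a fixed decision rule and the hypothesis it is meant to test. At 264 analysed patients and f(V) = 0.20, the criterion is met about 95% of the time whichever arm departs and in whichever direction, so it cannot separate benefit from harm or a training-specific effect from a general app effect. The level of 95% rests on that effect size and, in the simulation, on an assumed correlation of 0.5 and equal SDs. The equality across scenarios does not. Power for the two contrasts is unstated and depends on the effect pattern, so a shortfall is not shown. Because the post-hoc tests would probably expose a misleading interaction, this is a correction worth making before analysis, not a defect that invalidates the trial.

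**What to change.** Reword the criterion in the Statistical Analysis section:
- Efficacy, as a claim of training-specific benefit, requires lower weekly mean drinking in Group A than in Group B and than in Group C, each tested two-sided at 0.05. Both must succeed, so alpha need not be split.
- Name the post-baseline assessment, or the average of post-baseline assessments, on which the contrasts are made.
- Keep the interaction as supportive, or as a gate if the authors prefer. As a gate it costs some power (0.968 to 0.940 at d = 0.5; 0.843 to 0.752 at d = 0.4).
- Report B versus C, so that a difference between sham and treatment as usual is visible.
- State power for A versus B and A versus C beside the omnibus figure, with the assumed effect pattern.

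The cost is a change of wording and a restated power figure. Recruitment, arms and data collection stay as they are.

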### Measures

Upon admission to the study, patients in all three or the groups will be assessed in a baseline interview. Details about patients' socio-demographic characteristics, AUD diagnosis, treatment goals, and pharmacological treatment will be obtained from their clinical records (54–56). At baseline, the general premorbid intelligence level and cognitive functioning will be assessed. Experimental measures of patients' cue-induced cravings, alcohol AB, action-tendency bias, inhibition bias, and cognitive flexibility (24, 26, 27, 57, 58) will be administered at baseline and post-treatment. Clinical measures of patients' alcohol consumption (the primary outcome measure), cravings, self-efficacy, and affective states (the secondary outcome measures) (57–62) will be taken at the baseline, post-treatment, and follow-up assessments. The follow-ups will be given at 3- and 6-months post-treatment.

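### The stated sample sizes do not follow from their printed inputs: 264 is the N for power 0.95, not 0.90, and the dosage inputs do not give 220

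*Protocol article*

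**What the plan says.** All the figures are in the Statistical Analysis section of the protocol article.

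- **Main calculation.** The test is a "repeated-measures MANOVA with α = 0.05", with "effect size (ES) of *f* =0.20", power 0.90, three groups and four time-points. The result reads "time-points measurements = 4. It showed that 88 participants will be required for the final analyses in each of the four cells", with a total of 264. Since 264 / 88 = 3, the 88 is per randomised group.
- **Effect tested.** "Efficacy would be indicated by a significant Time X Study Group interaction".
- **Dosage calculation.** A MANOVA with special effects and interactions: alpha 0.05, f²(V) = 0.06, power 0.90, k = 3, then "predictors = 3; and response variables = 8), which yielded an" N of 220.
- **Enrolment.** 264 is increased by 20% for attrition, giving 317.

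**The concern.** The article prints both the inputs and the results of two power calculations, so each can be checked directly. If a result does not follow from its inputs, the stated power, the stated N or one of the inputs is wrong, and a reader cannot tell which. The main calculation matters more, because the enrolment target of 317 is built on 264 and the trial is presented as having 90% power. The dosage calculation supports a secondary hypothesis and does not drive enrolment.

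**Working it through.** **Method.** Noncentral-F power for Pillai's V, as used for MANOVA designs. Two noncentrality conventions are in common use, and both are shown: O'Brien-Shieh, λ = s·N·f², and Muller-Peterson, λ = df2·f². Neither needs a correlation among repeated measures, which fits the article, since it states none.

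**Main calculation**

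Inputs (Statistical Analysis section): alpha = 0.05, f = 0.20 so f² = 0.04, k = 3, m = 4, Time x Group interaction.

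- s = min(k−1, m−1) = min(2, 3) = 2
- df1 = (k−1)(m−1) = 2 × 3 = 6
- df2 = s(N − k − (m−1) + s) = 2(N − 3 − 3 + 2) = 2(N − 4)
- At N = 264: df2 = 520; λ = 2 × 264 × 0.04 = 21.12 (O'Brien-Shieh) or 520 × 0.04 = 20.80 (Muller-Peterson)

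| N | Power, O'Brien-Shieh | Power, Muller-Peterson |
|---|---|---|
| 220 | 0.899 | 0.892 |
| 221 | 0.900 | 0.894 |
| 225 | 0.906 | 0.900 |
| 254 | 0.941 | 0.937 |
| 263 | 0.949 | 0.946 |
| 264 | 0.950 | 0.947 |

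The smallest N for power 0.90 is 221 (222 in equal groups, 74 each) or 225 (75 each). The smallest N for power 0.95 is 264 or 268. The plan's 264, with its 88 per group, is therefore reproduced exactly under O'Brien-Shieh, but at power 0.95.

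The 254 row is the number of completers left if 20% of 317 are lost: 317 × 0.80 = 253.6.

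**Could another procedure give 264 at power 0.90?** A between-groups repeated-measures test with f = 0.20 needs 201 at a correlation of 0.5. It reaches about 264 only at a correlation of about 0.76 to 0.77, which the article does not state, and it is not the interaction that the article names. The univariate repeated-measures interaction test needs far fewer, 57 to 111 for correlations from 0.5 down to 0.

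**Dosage calculation**

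Inputs as printed: alpha = 0.05, f²(V) = 0.06, k = 3, q = 3 predictors, p = 8 responses.

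- s = min(p, q) = 3
- df1 = p·q = 24
- df2 = s(N − k − p + s) = 3(N − 3 − 8 + 3) = 3(N − 8)

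| Predictors | N for 0.90 (O'Brien-Shieh / Muller-Peterson) | N for 0.95 | Power at N = 220 |
|---|---|---|---|
| 3 (as printed) | 162 / 170 | 189 / 196 | 0.980 / 0.975 |
| 2 | 208 / 217 | 244 / 253 | 0.920 / 0.906 |

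As printed, the inputs do not give 220 at power 0.90, nor at 0.95, so the apparent slip in the main calculation does not explain this one. Rounding of f²(V) does not explain it either: by O'Brien-Shieh, 0.055 gives 176 and 0.0625 gives 156. With two predictors (k − 1 for three groups), Muller-Peterson gives 217, close to 220. With two predictors and k = 6 it gives exactly 220, but k = 6 is not what is printed.

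**The case against.** The strongest reply is that nothing harmful follows. Both printed sample sizes exceed what their inputs require at power 0.90, and after 20% attrition the main test still has power of about 0.94. On this view 264 is a sound result beside a misprinted power. That stands as to consequence: this is an error in the stated justification, and the design is not underpowered for the test it was sized on. It does not remove the error, because 264 is the basis of the enrolment target and the power attached to it is not the one it delivers.

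It is also fair to say that the dosage N cannot be corrected from the document alone. A reader might infer that 220 must become 162 to 170. That assumes the printed count of three predictors is right. With two predictors the required N is 208 to 217, so the document shows only that inputs and N disagree.

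A reader might also infer a power shortfall for alcohol attentional bias. The Measures section has it "alcohol AB, action-tendency bias, inhibition bias, and cognitive flexibility (24, 26, 27, 57, 58) will be administered at baseline and post-treatment" only, while the calculation uses four time-points, and at f = 0.20 with two time-points power is about 0.82 at 254 completers. The document does not support calling this an error. The primary outcome, weekly mean drinking, is assessed at all four time-points, so four is the right input. The attentional-bias effects that the article cites are also larger (f = 0.30, 0.33 and 0.39). Even at the smallest, f = 0.30, two time-points and 254 completers give power of about 0.99.

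**Conclusion.** The concern holds as a mismatch between printed inputs and printed results.

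- **Main test.** Power 0.90 needs 221 to 225, against 264 stated. The excess is 39 to 43 patients (264 − 225 and 264 − 221). The stated N corresponds to power 0.95 (0.947 to 0.950 across the two conventions). This assumes the MANOVA Time x Group procedure, which the article names, and f on the f(V) scale of that procedure. That 0.95 was entered and 0.90 reported is an inference from the exact match, not something the document says.
- **Dosage test.** The printed inputs give 162 to 170, against 220 stated. Which element is misprinted is not established.

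Both discrepancies run in the conservative direction. They are no ground for saying that the trial is underpowered or that its enrolment target is too small for the main test.

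**What to change.** 1. Restate the main calculation as power 0.95 with N = 264 (88 per group), or as power 0.90 with N = 222 to 225 (74 to 75 per group). The first keeps every downstream figure unchanged.
2. Check the dosage calculation against its original G*Power output, identify whether the predictor count, another input or the N is misprinted, and correct it so that inputs and N agree.

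The cost is two re-run calculations and a few corrected figures in one paragraph. Enrolment, design and analysis stay as they are.
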